#### Primary outcomes

The primary outcomes are the average daily sedentary time during work hours and the average number of breaks per day. These will be measured over a 7-day period immediately prior to randomization and at the completion of the intervention period. Sedentary time will be measured using an accelerometer (ActiGraph GT3XP, ActiGraph, Pensacola, FL, USA) and participants will be required to keep a log of work hours during these measurement periods. Following this period all data will be downloaded and analyzed. The ActiGraph accelerometer is a small, lightweight, plastic device worn around the waist. It measures motion data using three axes. This device is reliable and provides stable measurements of physical activity when compared to other measures of physical activity
[29].

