#### Sample size calculations

We did not conduct a formal power analysis to determine sample size, since the threshold for defining harmful levels of sitting is unknown. The proposed sample size of this study is similar to previous pilot studies of workplace sitting and sedentary time. Our sample of 60 participants (three groups of 20 participants) should be sufficient for assessing the direction of intervention effects, while taking into account possible missing data and participation attrition.

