#### Randomization and blinding

Participants will be randomly allocated into one of three study groups. A researcher who is not involved in participant recruitment or data collection will produce a randomly generated sequence for allocating participants to one of the three groups. This will be done prior to commencement of the trial. This researcher will prepare consecutively numbered sealed opaque envelopes that contain the group allocation for each individual participant. The envelope for each participant will be opened after the participant has enrolled in the study and after baseline data is collected. The randomization sequence will contain equal numbers of subjects in each group but will be otherwise unrestricted.

Data collection will take place away from the participants’ office and data collectors will be instructed not to enter the office areas of participants. This will ensure blinding of the data collectors to allocation of participants to the sit-stand desk intervention group. The office set-up in the workplace setting for this trial is predominantly private, single occupier offices with few work centers using open-plan office design. This feature of the study setting will assist with limiting the exposure of participants to the other trial interventions and ensure blinding of the data collectors to treatment allocation.

Participants will be kept naive as to the main aim of the study, that is, reduction of unhealthy sitting behaviors. This is because it is believed by the research team that participants being aware that the primary outcome is to reduce sitting behavior might actually change this behavior. Participants will also be blinded where possible to the intervention groups to which they are not allocated. Knowledge of the other interventions that are being tested, both clearly being interventions designed to reduce sitting behavior, might also impact on the sitting behavior of participants. Participants will therefore be informed that they are participating in a trial of general workplace health interventions and remain blinded to the other intervention groups.

A researcher who is blinded to the participant allocation will perform data entry and analysis.

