#### Statistical methods

Accelerometer activity counts will be recorded in 1-second intervals and aggregated into 1-minute epochs. We will download ActiGraph data using ActiLife proprietary software and conduct further processing with a custom macro to categorize the data into activity intensity categories: sedentary (<100 counts/minute), light (101 to 2,020 counts/minute), moderate (2,021 to 5,999 counts/minute), and vigorous (≥6,000 counts/minute), based on the frequently used sedentary cut-point for ActiGraph accelerometers
[37] and National Health and Nutrition Examination Survey (NHANES) cut-points for light, moderate, and vigorous intensity levels
[38]. Spurious epochs will be defined as over 20,000 counts/minute
[39], and non-wear time will be defined as periods of consecutive strings of zero-count epochs lasting at least 60 minutes. A whole day of monitoring will be considered as valid if the participant wears the accelerometer for at least 10 hours during their waking time. A workday will be considered valid if the participant wears the accelerometer for at least 75% of their time at work
[40].

We will conduct two-way repeated measures analyses of variance (rANOVA) to compare participants’ objectively assessed time spent in sedentary, light, and moderate-to-vigorous intensity physical activity, as well as their self-reported sitting time, musculoskeletal symptoms, and workability pre- and post-intervention. The two-way rANOVA will have one group factor (education; education plus sit-stand desk; control) and one time factor (pre- and post-intervention). Models will test for group and time main effects and group X time interactions to examine whether any differences in outcome variables vary by study group from pre- to post-intervention.

The primary analysis will be by intention-to-treat. All analyses will be conducted using IBM SPSS Statistics for Windows Version 21.0 (IBM, Armonk, NY, USA).

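### The pre/post repeated measures ANOVA lists a halved group effect and a non-randomised time effect as tests, and its one treatment test is less precise than baseline-adjusted ANCOVA

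*Protocol article*

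**What the plan says.** Under Statistical methods, the protocol article specifies a two-way repeated measures ANOVA with a three-level group factor (education, education plus desk, control) and a two-level time factor (before and after the intervention). It applies this to the accelerometer intensity categories, self-reported sitting time, musculoskeletal symptoms and workability. The tests are listed in one sentence: "Models will test for group and time main effects and group X time interactions", and the sentence gives their purpose as "to examine whether any differences in outcome variables vary by study group from pre- to post-intervention". None of the three tests is named as the one that decides whether an intervention works, and no baseline covariate is included.

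Under Primary outcomes, the timing is fixed: "These will be measured over a 7-day period immediately prior to randomization and at the completion of the intervention period". Each participant therefore has one value before randomisation and one after.

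Two other sections bear on the point. Sample size calculations states "We did not conduct a formal power analysis to determine sample size" and sets 20 participants per group. Randomization and blinding states "The randomization sequence will contain equal numbers of subjects in each group but will be otherwise unrestricted", so nothing in the design balances baseline sitting time across groups.

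**The concern.** The listed tests do three different jobs, and only one of them answers the trial's question.

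- **Group main effect.** It compares arms on the average of the pre and post values. Randomisation makes the expected pre difference zero, so the test targets half the treatment effect.
- **Time main effect.** It averages change over all three arms, control included. A shift common to everyone, for example from wearing the monitor a second time, would make it significant with no intervention effect at all.
- **Interaction.** This is the treatment test, but in a two-time-point design it uses the baseline only by subtracting it. That is less efficient than regressing on it.

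Two things are at stake. A trial of 20 per arm without a power calculation gives up precision it could have from data already collected. A null group effect or a significant time effect could also be reported as evidence about the interventions, because the plan does not say otherwise.

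**Working it through.** The plan states no power or effect size, so there is no figure of its own to reproduce.

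**Inputs from the protocol article.** Three arms, n = 20 per arm, N = 60 (Sample size calculations); one pre-randomisation and one follow-up value (Primary outcomes).

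**Assumptions.** The article does not give these: two-sided alpha 0.05, complete data, SD = 1 at both times, pre-post correlation r from 0.3 to 0.9, true follow-up difference d in SD units.

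**Step 1: what each test estimates.** For a pairwise comparison each variance below is multiplied by 2/n = 0.1.

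| Test | Expected value | Variance factor |
|---|---|---|
| Group main effect, (pre+post)/2 | d/2 | (1+r)/2 |
| Interaction, post − pre | d | 2(1−r) |
| ANCOVA, post given pre | d | 1−r² |

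Estimating the ANCOVA slope adds a finite-sample factor of 1 + 1/(60−3−2) = 1 + 1/55 = 1.018.

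**Step 2: ANCOVA against the interaction.** The ratio is (1−r²) / [2(1−r)] = (1+r)/2. The number per arm at which the interaction matches ANCOVA with 20 is 20 / [(1+r)/2].

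| r | Ratio | Ratio × 1.018 | Matching n per arm | Extra participants |
|---|---|---|---|---|
| 0.3 | 0.65 | 0.66 | 30.8 | 54% |
| 0.5 | 0.75 | 0.76 | 26.7 | 33% |
| 0.7 | 0.85 | 0.87 | 23.5 | 18% |
| 0.9 | 0.95 | 0.97 | 21.1 | 5% |

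The last two columns use the large-sample ratio. With the 1.018 factor the extra participants become about 51%, 31%, 16% and 3%. The break-even point is (1+r)/2 × 1.018 = 1, which gives r of about 0.96.

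**Step 3: where the lost precision goes.** 2(1−r) = (1−r²) + (1−r)². The second term is the variance contributed by chance baseline imbalance. With 20 per arm, the standard error of a pairwise baseline difference is √(2/20) = 0.32 SD. A difference of that size shifts the change-score contrast by (1−r) × 0.32, which is 0.16 SD at r = 0.5. ANCOVA removes that shift.

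**Step 4: group main effect against the interaction.** The ratio of noncentralities is [(1/4) / ((1+r)/2)] / [1 / (2(1−r))] = (1−r)/(1+r), which is 0.54, 0.33 and 0.18 at r = 0.3, 0.5 and 0.7.

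**Step 5: pairwise power at d = 0.8.** Noncentral t, with 57 error df for the ANOVA contrasts and 56 for ANCOVA. Worked for r = 0.5:

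- Main effect: 0.4 / √(0.75 × 0.1) = 1.46, power 30%.
- Interaction: 0.8 / √(1.00 × 0.1) = 2.53, power 70%.
- ANCOVA: 0.8 / √(0.75 × 1.018 × 0.1) = 2.90, power 81%.

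At r = 0.3 the three powers are 34%, 56% and 73%. At r = 0.7 they are 27%, 89% and 93%.

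**Step 6: overall three-arm tests.** 3,000 simulated trials per setting, with 2-df F tests and true effects of 0, 0.4 and 0.8 SD reduction:

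| r | Group main effect | Interaction | ANCOVA |
|---|---|---|---|
| 0.3 | 26% | 45% | 63% |
| 0.5 | 24% | 60% | 73% |
| 0.7 | 21% | 84% | 87% |
| 0.9 | 19% | 100% | 100% |

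With no effect in any arm, all three tests rejected in 4% to 5% of trials.

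**Step 7: unequal SDs.** With SDs s₁ and s₂ before and after, the change-score variance minus the ANCOVA variance is (s₁² + s₂² − 2r s₁s₂) − s₂²(1−r²) = (s₁ − r s₂)², which is never negative. The direction of the result therefore does not depend on equal SDs; its size does.

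**The case against.** The strongest reply is that the purpose clause, "to examine whether any differences in outcome variables vary by study group from pre- to post-intervention", describes the interaction. On that reading the main effects are only the usual listing of terms in a two-way model, and nobody has called them effectiveness tests. The interaction is unbiased over randomisation and holds its type I error, so the plan contains no invalid test. The fair comparison is then interaction against ANCOVA, where the gain depends on a correlation the article does not give and almost disappears when r is high. ANCOVA is also not entirely free: it uses one error df and assumes a common linear slope. Finally, the article calls the study a pilot and claims only that "Our sample of 60 participants (three groups of 20 participants) should be sufficient for assessing the direction of intervention effects".

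Much of this stands. The loss is of precision, not of validity, and baseline imbalance is the source of that loss rather than a separate bias. The purpose clause does point to the interaction, so the low power of the group main effect does harm only if someone reads that test as the treatment effect.

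It does not remove the point. The plan lists three tests and ranks none. The df cost moves the t critical value only from 2.002 to 2.003, and estimating the slope adds about 1.8% to the variance. A small pilot has more need of precision, not less, and the article's Discussion says the study will determine comparative effectiveness and inform guidelines and policy.

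**Conclusion.** The concern holds. As specified, the group main effect estimates half the treatment effect, the time main effect is not a randomised comparison, and the interaction is a change-score analysis. Replacing the interaction with ANCOVA cuts the variance by about 34%, 24%, 14% and 3% at r = 0.3, 0.5, 0.7 and 0.9, after charging for the estimated slope. In the three-arm scenario that moves power from 60% to 73% at r = 0.5 and from 84% to 87% at r = 0.7. These sizes rest on assumed correlations and effects, equal SDs and complete data; the algebraic results in steps 1 and 2 do not depend on the assumed values of r and d. This is a change the plan should make, but the trial is not invalid without it. The argument covers continuous outcomes and does not directly extend to the 7-day prevalence of musculoskeletal symptoms.

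**What to change.** In Statistical methods, replace the repeated measures ANOVA for continuous outcomes with ANCOVA: the follow-up value modelled on group, with the baseline value of the same outcome as covariate. A mixed model that constrains the baseline mean to be common to all groups is an equivalent choice. State that the group contrasts from this model are the treatment comparisons, report them as adjusted differences with 95% confidence intervals, and drop the group and time main effects as tests of effectiveness. If the repeated measures model is kept for any reason, say explicitly that only the interaction is read as evidence of treatment effect. Symptom prevalence needs its own model.

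The cost is a change of wording and one error df. The baseline is already collected before randomisation, and the method is available in the software the article names. Recruitment was still open when the article was submitted, so the change could be made before analysis.

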### Participants

Sixty participants will be recruited by advertisement from academic and administrative staff at the Faculty of Health Sciences, The University of Sydney. Posters will be placed in staff tearooms and common areas, inviting staff to participate in 'The Healthier Office Study’. The advertisements will contain general information informing participants that we are testing simple occupational health interventions and that participants will be provided with an ergonomic device or advice about improving healthy work practices. The advertisements will not contain specific detail about the interventions in order to keep the participants blinded to the interventions that they do not receive. The study will also be advertised in a short presentation at Faculty staff meetings to improve potential participants’ awareness of the study.

Participants will be included in the study if they are currently employed in a full-time academic or administrative role that involves greater than 15 hours per week or greater than 4 hours per day of computer-based work. The number of hours spent performing desk or computer duties will be determined for the purpose of inclusion in the study by self-report. Participants will be excluded if they have planned leave during the study period, any self-reported chronic illness, any self-reported musculoskeletal condition, or if they have a current worker’s compensation claim.

Data collection will involve the participant completing standardized assessment forms developed for this study. The assessment forms were piloted prior to commencement of the study to check for readability and participant burden. It was established that data collection for each participant involved less than 10 minutes of participant’s time. Missing data will be collected by telephone or email contact with the participant.

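### Unless data are complete or imputed, the planned repeated measures ANOVA is a completers' change-score analysis under an intention-to-treat label, and a baseline-adjusted mixed model would be more robust and more precise

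*Protocol article*

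**What the plan says.** All statements are in the protocol article.

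- Statistical methods, model: "We will conduct two-way repeated measures analyses of variance (rANOVA) to compare participants’ objectively assessed time spent in sedentary, light, and moderate-to-vigorous intensity physical activity". Self-reported sitting time, symptoms and work ability go through the same model. The design has "one group factor (education; education plus sit-stand desk; control) and one time factor (pre- and post-intervention"), and the group-by-time interaction is the test of whether change differs between groups.
- Statistical methods, principle and software: "The primary analysis will be by intention-to-treat", and "All analyses will be conducted using IBM SPSS Statistics for Windows Version 21.0". The SPSS procedure is not named, the intention-to-treat set is not defined, and no imputation is mentioned. The article does not say that incomplete participants will be excluded.
- Sample size calculations: the 60 participants were chosen "while taking into account possible missing data and participation attrition". No rate is given.
- Participants: "Missing data will be collected by telephone or email contact with the participant". This closes a paragraph about the assessment forms.
- Primary outcomes, and Randomization and blinding: the baseline accelerometer week precedes randomization, so loss after randomization falls mainly on the follow-up week.

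**The concern.** The article fixes both an estimation method and an analysis principle, and the method does not by itself deliver the principle once follow-up data are missing. A participant without a valid follow-up accelerometer week has no change score and adds nothing to the interaction test.

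The plan expects such gaps, and its own rules can create them. A workday counts only if the device was worn for at least 75% of work time, so a person can complete follow-up and still have no usable primary outcome. Telephone or email contact can recover a questionnaire answer but not a week of device wear.

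Two things are at stake. First, a change-score analysis of completers is biased if, for example, the heaviest sitters leave one arm more often than another. Second, even with no missing data, raw change scores use the baseline less efficiently than an analysis that conditions on it. With 20 people per arm, that efficiency matters.

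**Working it through.** **Inputs.** From the article: three groups of 20, two time points, baseline before randomization. The article gives no SD, no pre-post correlation and no missing rate. Those are assumptions below, shown over a range, with the outcome in SD units.

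**Step 1. The plan's own figure.** 3 × 20 = 60 checks. No power calculation lies behind it, so there is nothing further to reproduce.

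**Step 2. What the interaction test is.** With two time points, the group-by-time F equals the one-way ANOVA F on post minus pre. On simulated data with three groups of 20, both gave F = 2.1614. Only people with both values enter the test.

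**Step 3. How likely incomplete data are.** If each person lacks a value with probability p, the chance that at least one of 60 is incomplete is 1 − (1 − p)^60.

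| p | chance of at least one incomplete |
|---|---|
| 2% | 70% |
| 5% | 95% |
| 10% | 99.8% |

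Expected completers at 5%, 10%, 20% and 30% missing are 57, 54, 48 and 42 of 60.

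**Step 4. Precision.** With equal variances and correlation ρ, the per-person variance is 2(1 − ρ) for a change score and 1 − ρ² after baseline adjustment. The ratio is (1 − ρ²) / [2(1 − ρ)] = (1 + ρ)/2. (This ignores the small cost of estimating the slope.)

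| ρ | change score | baseline-adjusted | ratio | variance reduction |
|---|---|---|---|---|
| 0.3 | 1.40 | 0.91 | 0.65 | 35% |
| 0.6 | 0.80 | 0.64 | 0.80 | 20% |
| 0.8 | 0.40 | 0.36 | 0.90 | 10% |

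**Step 5. Bias.** Suppose that loss in an intervention arm depends on baseline sedentary time, with a logit slope of 1 per SD, and that loss in control is at random. Given baseline x (in SD from its mean), expected change is the true effect minus (1 − ρ)x. If the retained intervention participants have mean baseline m, the change contrast is therefore biased by −(1 − ρ)m. Integrating over a normal baseline gives m = −0.165 SD at 19% loss.

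| loss in intervention arm | m | bias, ρ = 0.3 | bias, ρ = 0.6 | bias, ρ = 0.8 |
|---|---|---|---|---|
| 10% | −0.091 | 0.06 | 0.04 | 0.02 |
| 19% | −0.165 | 0.12 | 0.07 | 0.03 |
| 30% | −0.253 | 0.18 | 0.10 | 0.05 |

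The bias is positive, so a reduction in sitting is understated when heavy sitters leave. It reverses if light sitters leave. Conditioning on baseline brings it to below 0.001 SD (checked by simulation at ρ = 0.6).

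**Step 6. The same effect in minutes.** A simulation used assumed values: SD 60 min, ρ = 0.5, true effect −60 min, 20 per arm, and about 28% loss in one arm depending on baseline against 10% at random in the other. Completers' change scores averaged −51.9 min and a likelihood analysis of all randomized participants averaged −60.0 min. With 20% missing completely at random, both were unbiased (−60.4 and −60.3).

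**Step 7. Where the gain comes from.** When baseline is complete, a mixed model with a common baseline mean and unstructured covariance gives the same contrasts as ANCOVA on completers. In four simulated trials of 60 with 48 to 52 completers, all eight contrasts agreed to about seven decimals. The gain comes from conditioning on baseline, not from keeping people who have only one measurement.

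**The case against.** The strongest reply is that the article contradicts nothing. Intention-to-treat also means analysis by allocated group, which this ANOVA respects. The text does not choose the SPSS repeated measures procedure that drops incomplete cases, and it does not exclude imputation or SPSS MIXED. How missing data are handled is commonly left to a full protocol or analysis plan that is not shown. This stands to the extent that a reader who infers that the two statements are incompatible, or that a complete-case analysis is certain, goes beyond the text. It does not dispose of the point, because the article names the model, and an analysis plan that followed it literally would inherit both the completers' restriction and the inefficiency.

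A second tempting inference is that the ANOVA costs power through dropout. At an assumed 15% loss (17 per arm), the difference detectable with 80% power at two-sided 5% rises from 0.91 to 0.99 SD. That rise comes from the missing follow-up itself. Baseline precedes randomization, so a mixed model keeps such people in the analysis set but learns almost nothing from them about the treatment contrast. The figure is no argument against the ANOVA.

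Third, the bias is small. At ρ = 0.6 with 17 and about 16.2 completers, the standard error of the change contrast is √[0.8 × (1/17 + 1/16.2)] = 0.31 SD, so 0.07 SD is under a quarter of one standard error. The intervention lasts 4 weeks, people with planned leave are excluded, and the stated aim is only that the sample "Our sample of 60 participants (three groups of 20 participants) should be sufficient for assessing the direction of intervention effects". All of this is fair. The precision gain, however, needs no missing data at all.

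**Conclusion.** The point holds in a limited form. As described, the group-by-time test compares change scores among people with both measurements. It covers every randomized participant only if data are complete or imputed. Otherwise it is a completers' analysis that is unbiased only if loss does not depend on baseline or outcome differently by arm.

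The avoidable cost in precision is about 35%, 20% or 10% of the contrast variance at ρ = 0.3, 0.6 or 0.8. The avoidable bias is about 0.12, 0.07 or 0.03 SD in the 19% scenario. The precision figures rest on equal variances and the assumed correlation. The bias figures also rest on an assumed loss rate, slope and difference between arms, none of which the article gives. If loss is completely at random there is no bias to remove. If loss depends on the unseen follow-up value, baseline adjustment alone does not remove the bias, and a sensitivity analysis is needed.

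**What to change.** For the primary accelerometer outcome, replace the ANOVA with a linear mixed model (SPSS MIXED) on all randomized participants as allocated. Use the before and after values as the response, with one common baseline mean, a separate follow-up mean for each group and an unstructured covariance. Report the between-group differences at follow-up. State that this is equivalent to ANCOVA when baseline is complete, and define the intention-to-treat set in one sentence.

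Add one sensitivity analysis that shifts missing follow-up values in the intervention arms toward control.

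The cost is some analysis-plan wording and slightly more analysis work in the software already named. Recruitment, measurement and participants are unaffected. The change should not be presented as recovering power lost to missing follow-up.
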